# Detection of residual consciousness using EEG indicators related to rectal perception: protocol for a diagnostic accuracy study

**DOI:** 10.3389/fneur.2026.1802303

**Published:** 2026-05-20

**Keywords:** diagnosis, disorders of consciousness, gut-brain axes, interoception, rectum

## Abstract

**Introduction:**

Accurate diagnosis of disorders of consciousness (DoC), including unresponsive wakefulness syndrome (UWS) and minimally conscious state (MCS), remains a long-standing and unresolved challenge in clinical practice. Current diagnostic frameworks rely predominantly on behavioral responsiveness, with the Coma Recovery Scale–Revised (CRS-R) serving as the clinical gold standard. However, behavior-based evaluation is intrinsically vulnerable to examiner subjectivity and cognitive–motor dissociation, contributing to misdiagnosis rates of up to 40%. From a theoretical perspective, consciousness comprises both external awareness and self-awareness, yet existing DoC assessments focus almost exclusively on external sensory processing, leaving self-awareness substantially underassessed. This imbalance highlights a critical gap that motivates for complementary assessment approaches targeting underexplored dimensions of consciousness.

**Methods and analysis:**

This study protocol aims to develop an EEG-based paradigm and evaluate its feasibility for assessing gut-related interoceptive processing in patients with DoC, using controlled, non-invasive rectal balloon distension. Standardized stimulation procedures, synchronized EEG acquisition, and predefined analytical pipelines will be implemented to characterize the temporal and spatial features interoceptive event-related potentials.

**Results:**

Electrophysiological and statistical analyses will be conducted to assess the feasibility, signal characteristics, and response profiles of gut-related interoceptive EEG activity across diagnostic categories. Exploratory analyses will further examine associations between interoceptive EEG markers and clinical behavioral measures.

**Discussion:**

By systematically investigating an under assessed dimension of consciousness, this study protocol aims to establish the feasibility and signal-level characteristics of gut-related interoceptive EEG responses in patients with disorders of consciousness. By providing methodological and exploratory evidence at the group level, the findings are intended to inform the design of future hypothesis-driven and validation studies, and to support the longer-term development of complementary assessment approaches that extend beyond behavior-based evaluation, with potential relevance for clinical research and public health-oriented diagnostic strategies.

**Clinical trial registration:**

[ClinicalTrials.gov], identifier [NCT07208942].

## Introduction

1

Disorders of consciousness (DoC), including unresponsive wakefulness syndrome (UWS) and minimally conscious state (MCS), represent devastating sequelae of severe brain injuries such as traumatic brain injury, stroke, and cardiac arrest. Advances in neurosurgery and critical care have increased survival following life-threatening brain insults; however, many patients progress to prolonged DoC, a condition associated with high mortality, severe disability, and substantial long-term care needs. As a result, DoC imposes profound physical, emotional, and economic burdens on patients’ families, healthcare systems, and society at large, contributing to a growing global population of affected individuals (1, 2). Epidemiological data indicate that approximately 4,200 new cases of UWS occur annually in the United States, while the incidence of MCS remains uncertain. Depending on diagnostic criteria, the prevalence of UWS is estimated to range from 5,000 to 42,000 individuals, whereas MCS prevalence may reach 112,000 to 280,000 individuals (3, 4). The lifetime cost of care for individuals with prolonged DoC can exceed $1,000,000 (5). Given China’s large population base, the public health burden associated with prolonged DoC is expected to be substantial. Despite this substantial burden, accurate diagnosis and clinical stratification of DoC remain among the most complex challenges in modern neurology.

The clinical classification of DoC relies predominantly on standardized behavioral assessments, with the Coma Recovery Scale–Revised (CRS-R) serving as the most widely used and validated diagnostic gold standard (6–8). The CRS-R evaluates behavioral responses to external sensory stimulation across six domains—auditory, visual, motor, oromotor, communication, and arousal—enabling differentiation between UWS, characterized by the absence of behavioral evidence of awareness, and MCS, defined by inconsistent but reproducible signs of conscious processing. Its strong psychometric properties have made it central to prognosis, treatment planning, and research enrollment (9, 10).

Nevertheless, behavior-based assessments are subject to important limitations. Their accuracy depends heavily on examiner expertise, and even trained clinicians may demonstrate inter-rater variability when scoring CRS-R items (11). More critically, cognitive–motor dissociation (CMD)—a condition in which patients retain conscious awareness but lack the motor capacity to express it—can lead to systematic underestimation of consciousness based solely on observable behavior (12). Reported misdiagnosis rates in DoC populations range from 37 to 43%, with CMD affecting approximately 8% of coma patients, 7% of UWS patients, and up to 20% of patients classified as MCS minus (MCS−) (11, 13, 14). This means one in five MCS patients may have their true level of consciousness substantially underestimated based solely on behavioral observations. Such diagnostic inaccuracies have profound ethical and clinical consequences, potentially denying patients appropriate rehabilitation opportunities or leading to unsuitable treatment decisions.

To overcome the limitations of behavioral assessments, neuroimaging techniques such as functional magnetic resonance imaging (fMRI) and fluorodeoxyglucose positron emission tomography (FDG-PET) have been increasingly employed to detect covert consciousness—neural evidence of awareness not apparent at the bedside (15–19). Although these modalities have demonstrated value in selected cases, their routine clinical use is constrained by high costs, operational complexity, and limited accessibility, particularly in resource-limited settings. Practical challenges further restrict their feasibility in severely impaired patients. For instance, fMRI requires patients to maintain immobility for prolonged periods—a nearly insurmountable barrier for DoC patients with motor deficits or agitation. Additionally, FDG-PET relies on radioactive tracers and remains largely inaccessible in low and middle-income countries (LMICs). These limitations underscore the urgent need for objective, low-cost, and portable assessment tools that can complement existing diagnostic frameworks.

From a theoretical perspective, consciousness is widely conceptualized as comprising two interacting components: arousal and awareness. Awareness itself encompasses both external awareness of the environment and internal self-awareness (20, 21). While many patients with DoC retain arousal, as evidenced by preserved sleep–wake cycles, awareness is variably impaired. Current diagnostic paradigms, however, focus almost exclusively on external awareness, assessed through sensory responsiveness and command-following tasks, while self-awareness—a core aspect of subjective experience—remains largely unexamined in routine clinical practice (22).

Interoception, defined as the brain’s capacity to sense and integrate internal bodily signals such as cardiac, respiratory, and gastrointestinal activity, is increasingly recognized as a fundamental contributor to self-awareness (23–25). Alterations in interoceptive processing have been implicated in a range of neuropsychiatric and neurological disorders (26), and emerging evidence suggests that disrupted interoceptive signaling may also play a role in altered states of consciousness (23). To date, interoceptive research in DoC has focused primarily on cardiac-related measures, such as heartbeat-evoked potentials. However, these signals can be influenced by movement artifacts, medication effects, and autonomic instability, limiting their robustness in clinical settings (27–29).

The gastrointestinal system, by contrast, represents a major interoceptive organ that communicates with the brain through the gut–brain axis, involving the vagus nerve, enteric nervous system, and multiple neurochemical pathways (30). Gut-related interoceptive signals are physiologically salient and relatively stable, yet their potential relevance to DoC assessment has not been systematically explored.

Importantly, controlled visceral stimulation paradigms, such as rectal balloon distension, have been widely used in gastrointestinal and neurophysiological research to investigate interoceptive processing (31–33). Previous studies have demonstrated that such stimulation can reliably evoke cortical responses, including activations in the insular and anterior cingulate cortices, as well as time-locked electrophysiological responses measurable with EEG and evoked potential techniques (34, 35). These findings support the feasibility of using rectal distension as a controlled and reproducible approach to probe gut-related interoceptive signaling in humans.

Electroencephalography (EEG) offers a particularly suitable platform for investigating such processes, given its low cost, portability, high temporal resolution, and feasibility for bedside application in severely impaired patients.

Against this background, the present study protocol proposes an EEG-based interoceptive assessment paradigm using controlled, non-invasive rectal balloon distension to probe gut-related interoceptive processing in patients with DoC. Given the absence of standardized interoceptive paradigms in DoC populations, a rigorously defined protocol represents a necessary first step prior to hypothesis-driven or diagnostic validation studies. The present study is designed to examine the feasibility, signal characteristics, and descriptive group-level patterns of interoceptive EEG responses across diagnostic categories. By systematically investigating an underexplored dimension of consciousness, this work aims to provide foundational, hypothesis-generating evidence that may inform future validation studies and facilitate the development of complementary assessment approaches extending beyond behavior-based diagnostics.

## Methods and analysis

2

### Study design and setting

2.1

This study is designed as a prospective, observational, exploratory study. Its primary objective is to evaluate the feasibility, signal characteristics, and descriptive group-level electrophysiological patterns associated with gut-related interoceptive processing in patients with DoC, rather than to establish diagnostic accuracy or individual-level classification. The study is conducted in the General Department of Hyperbaric Oxygen at the Second People’s Hospital of Hefei (Hefei, China).

The center has established a specialized system covering diagnostic confirmation and comprehensive management, which includes standardized diagnostic workflows, a bedside electroencephalography (EEG) system (iRecorder W32), and a multidisciplinary clinical research team proficient in interoceptive testing and DoC research. Additionally, the controllable rapid inflation-deflation rectal stimulation device was independently developed by the research team (Figure 1). These resources ensure protocol adherence, data uniformity, and participant safety throughout the entire study period. The study will be reported in accordance with STARD-informed principles where applicable, with an emphasis on transparent reporting of study design, participant flow, and analytical procedures.

**Figure 1 fig1:**
[figure not shown]
Schematic diagram of the rectal balloon stimulation and electroencephalogram synchronous recording system: (1) A 32-channel scalp electrode cap: continuous acquisition of cortical electrical signals; (2) Stimulation control and data recording computer: customized software was run to set stimulation parameters and send synchronous trigger signals, and EEG responses were recorded at the same time; (3) Intestinal airbag precision charging and discharging control device: through the servo motor; (4) Drive screw module, precise control of gas injection and withdrawal; (5) Anorectal manometry catheter: the front end was connected with an expandable balloon, lubricated with paraffin oil and placed in the rectum.

### Participant enrollment

2.2

Participants will be recruited according to predefined inclusion and exclusion criteria (Table 1). The target sample size is 15 participants per group: unresponsive wakefulness syndrome (UWS), minimally conscious state (MCS), and age and sex-matched healthy controls (HCs). Written informed consent will be obtained from all participants or, for DoC patients, from their legal guardians prior to enrollment. Healthy control participants will be recruited from the local community and screened to exclude neurological, psychiatric, or gastrointestinal disorders.

**Table 1 tab1:** Inclusion and exclusion criteria for DoC and control individuals.

Patient group inclusion criteria	Patient group exclusion criteria
1. Patients with chronic-phase disorders of consciousness (DoC) (duration ≥28 days) due to etiologies such as traumatic brain injury, stroke, or cardiac arrest.	1. History of developmental psychiatric or neurological disorders causing functional impairment.
2. Age ≥18 years.	2. Untreated epilepsy.
3. Absence of acute complications such as fever or infection within 15 days prior to enrollment.	3. Untreated cerebral edema.
4. No use of sedative medications within 15 days prior to enrollment.	4. Unstable vital signs.
5. No use of any medications potentially affecting gastrointestinal motility within 7 days prior to testing.	5. History of intestinal diseases.
6. Written informed consent provided by family members or legal guardians.	6. History of abdominal surgery, except for simple appendectomy or cholecystectomy.
	7. Presence of organic diseases such as spinal cord injury or thyroid dysfunction.
	8. Patients with skull defects resulting in cranial depression, or those who have undergone cranioplasty with titanium alloy.

Control group inclusion criteria	Control group exclusion criteria
1. Age-matched, conscious healthy adults.	1. Failure to meet any of the above inclusion criteria.
2. No history of gastrointestinal diseases or abdominal surgery.	2. Unwillingness to provide written informed consent.
3. No history of psychiatric disorders.	
4. Cessation of any medications or foods affecting psychiatric or gastrointestinal function 48 h prior to the experiment.	
5. Written informed consent provided by the participant.	

Given that patients with DoC frequently present with a history of decompressive craniectomy or cranioplasty, additional criteria will be applied to ensure the quality and interpretability of EEG recordings. Patients with skull defects associated with significant cranial depression will be excluded, as such conditions may substantially distort electrophysiological signals. In addition, patients who have undergone cranioplasty using titanium implants will be excluded due to potential interference with EEG signal acquisition. In contrast, patients reconstructed with polyetheretherketone (PEEK) materials or autologous bone grafts will be considered eligible, as these materials are not expected to significantly affect EEG recording quality (36).

The study protocol has been registered on ClinicalTrials.gov (NCT07208942) and approved by the Ethics Committee of the Second People’s Hospital of Hefei (Approval No.: 2024-Research-170).

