### Data preprocessing and statistical analysis

2.6

EEG data will be preprocessed using EEGLAB (v2024.0) in MATLAB R2024b following a predefined pipeline. Continuous data will be band-pass filtered between 0.1 and 40 Hz and segmented into epochs time-locked to rectal distension onset (−200 to 800 ms). Independent component analysis (ICA) will be applied to identify and remove components associated with ocular, muscular, and cardiac artifacts, based on spatial topography, power spectra, and time-course characteristics.

Event-related potentials (ERPs) will be quantified at predefined fronto-central electrodes. ERP components of interest (N1, P2, and P3) will be defined within fixed latency windows based on prior interoceptive ERP literature (N1: 80–150 ms; P2: 150–250 ms; P3: 250–400 ms). Mean amplitude and peak latency within these windows will be extracted for statistical analysis.

Time–frequency analyses will be conducted using event-related spectral perturbation (ERSP) methods, with baseline normalization relative to the −200 to 0 ms pre-stimulus interval. Power changes in the theta (4–7 Hz) and alpha (8–12 Hz) bands will be quantified.

Group-level comparisons among UWS, MCS, and healthy control participants will be performed using one-way ANOVA for each predefined electrophysiological outcome. *Post hoc* pairwise comparisons will be corrected for multiple testing using the Tukey HSD procedure. Effect sizes (η^2^ or Cohen’s d, as appropriate) will be reported to inform the design of future confirmatory studies. All analyses will be restricted to predefined electrodes, frequency bands, and latency windows to limit multiple comparisons and reduce the risk of false-positive findings.

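### UWS, MCS and controls are compared by an unadjusted one-way ANOVA with no balancing of UWS against MCS; separately, the text and Table 1 disagree on how controls are matched and screened

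*Protocol article*

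**What the plan says.** Section 2.1 states the design: "This study is designed as a prospective, observational, exploratory study". Section 2.2 sets the size: "The target sample size is 15 participants per group", for UWS, MCS and healthy controls. Section 2.3 assigns patients to UWS or MCS from repeated CRS-R assessments. No section describes matching or stratifying the two patient groups against each other.

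On controls, the text of section 2.2 asks for "age and sex-matched healthy controls (HCs" who are "screened to exclude neurological, psychiatric, or gastrointestinal disorders". In Table 1 the matching criterion is "Age-matched, conscious healthy adults", and the history criteria are "No history of gastrointestinal diseases or abdominal surgery" and "No history of psychiatric disorders". Sex and neurological history do not appear in the control columns.

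Section 2.6 says that the three-group comparisons "will be performed using one-way ANOVA for each predefined electrophysiological outcome", followed by Tukey HSD pairwise tests. No covariate is named. The same section says that effect sizes will be reported to help design later confirmatory studies. Sections 2.5 and 2.7 label the group comparisons exploratory, and section 2.7 places them among the secondary outcomes.

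**The concern.** There are two separate points.

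First, group membership is observed and not assigned. Patients may be any age from 18 upwards and have mixed causes of brain injury, so UWS and MCS may differ in age or sex for reasons unrelated to the level of consciousness. The protocol treats age and sex as worth matching for controls, but neither the design nor the specified test handles them between the patient groups. The limitations in the Discussion name medication, autonomic dysfunction and gastrointestinal comorbidity as influences on interoceptive processing, but not age or sex. At stake is the UWS-MCS effect size, which a later study could be sized on.

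Second, section 2.2 says recruitment follows Table 1, and the first control exclusion in that table is failure to meet the listed criteria. Staff who apply the table literally have no sex-matching rule, and no neurological exclusion beyond the word healthy. Staff who follow the text have both. This bears on the control-UWS and control-MCS contrasts.

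**Working it through.** **The plan's own figure.** Inputs from section 2.5: d = 1.13, two-sided alpha 0.05, power 80%. By the normal approximation, n per group = 2 × (1.960 + 0.842)² / 1.13² = 2 × 7.85 / 1.277 = 12.3, so 13, as stated. By the exact t-test, power is 78.9% at 13, 82.1% at 14 and 84.8% at the target of 15. The stated figure is reproduced to within one participant. Here d = 1.13 serves only as a yardstick; section 2.5 does not say which pair of groups it came from.

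**Systematic imbalance.** If the outcome correlates r with age within groups, and the true mean ages of UWS and MCS differ by g SD, the unadjusted contrast is shifted by r × g outcome SDs. Neither r nor g is in the document; r = 0.2 to 0.5 and g = 0.5 to 1.0 are assumptions. The rates below come from 20,000 simulated studies per row, with three groups of 15 and no true group difference.

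| r | g (SD) | Spurious difference r × g (SD) | Share of 1.13 | Overall F-test | Tukey UWS-MCS, unadjusted | Tukey UWS-MCS, age-adjusted |
|---|---|---|---|---|---|---|
| 0.2 | 0.5 | 0.10 | 9% | 5.4% | 2.2% | 1.8% |
| 0.2 | 1.0 | 0.20 | 18% | 6.9% | 3.5% | 1.9% |
| 0.3 | 0.5 | 0.15 | 13% | 6.3% | 2.9% | 1.9% |
| 0.3 | 1.0 | 0.30 | 27% | 9.9% | 6.4% | 1.9% |
| 0.5 | 0.5 | 0.25 | 22% | 8.7% | 4.9% | 2.0% |
| 0.5 | 1.0 | 0.50 | 44% | 20.3% | 15.9% | 2.1% |

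With g = 0 the unadjusted Tukey contrast rejects in about 2% of runs and the F-test in about 5%, as they should. A sex difference would act in the same way, with a shift equal to the difference in sex proportions times the sex effect on the outcome.

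**Chance imbalance.** With 15 per group, the difference in mean age has standard deviation √(2/15) = 0.365 SD and a 95% range of ±1.96 × 0.365 = ±0.72 SD. The chance of a gap of 0.5 SD or more is about 17%. This is ordinary sampling variation; the g = 0 result shows that the ANOVA error term already allows for it.

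**Precision.** Residual degrees of freedom are 45 − 3 = 42, and 40 with age and sex added. With no systematic gap, and an outcome related to age only, the 95% interval width after adjustment relative to before is 1.02 at r = 0.1, 1.01 at 0.2, 0.98 at 0.3 and 0.94 at 0.4.

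**Controls, text against Table 1.**

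| Item | Text of section 2.2 | Table 1, control columns |
|---|---|---|
| Age matching | yes | yes |
| Sex matching | yes | absent |
| Psychiatric history | excluded | excluded |
| Gastrointestinal history | excluded | excluded |
| Neurological history | excluded | absent |

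Neither place says whether the 15 controls are matched to UWS, to MCS or to the pooled patients.

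**The case against.** The strongest reply is that the study is exploratory. The protocol disclaims diagnostic and causal conclusions, and a descriptive study may report the group differences it observes. That stands, and it limits the weight of the point. It does not remove it, because effect-size estimates are a declared product of the study and a confounded estimate misleads whoever plans from it, whatever the p-value. An analysis plan that is not shown might add covariates, but this document names a specific unadjusted test.

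Adjustment for age and sex would also leave cause of injury and time since injury untouched. That is true, and it is a reason to say so in the report.

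A reader might infer four stronger things that the document does not support:

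- **That the Table 1 mismatch confounds UWS against MCS.** It concerns controls only and cannot do so.
- **That the ±0.72 SD chance range is a bias.** It is not; the error term covers it.
- **That neurological screening and sex matching have been dropped from the plan.** The text requires both, and Table 1 says healthy; this is an inconsistency.
- **That matching fails because 15 controls cannot pair one-to-one with 30 patients.** The protocol never claims one-to-one matching, and matching at group level fits its wording.

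**Conclusion.** Both points hold, at modest weight.

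For UWS against MCS, nothing in the stated design or test removes a systematic age or sex difference. No such difference is shown to exist. Under the assumed ranges the consequence runs from negligible on error rates (0.10 SD, 2.2%) to material (0.50 SD, 15.9%), and no value within that range can be preferred from the document. The case for adjustment is protection of the effect size; the gain in precision is small, and absent at correlations of about 0.2 or below.

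For controls, the contradiction within section 2.2 is a matter of reading and needs no assumption. Its effect on the contrasts with controls cannot be sized from the document.

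**What to change.** 1. For each electrophysiological outcome, fit a linear model with group, age and sex. Report Tukey-type pairwise contrasts of the adjusted means beside the unadjusted one-way ANOVA.
2. Report age, sex, cause of injury and time since injury by group, and state that differences other than age and sex remain unadjusted. With 45 participants the model can carry few further covariates.
3. Reconcile the Table 1 control criteria with the text on sex matching and neurological history, and state which patient group or groups the 15 controls are matched to.

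The cost is two of 42 residual degrees of freedom, and intervals about 1% to 2% wider if the covariates are only weakly related to the outcome. If UWS and MCS do differ in age, the adjusted contrast also loses some precision because group and age overlap. At a gap of 1 SD, and before any fall in residual SD, the factor is about √[(2/15 + 1/42) / (2/15)] = 1.09. Age must be known to apply the entry criterion and both variables to match controls, so little or no new data collection should be needed. The third item is a short text edit.

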### Study workflow

2.3

Upon enrollment (Figure 2), all DoC patients will undergo standardized CRS-R assessments administered at least five times over a one-week period by a trained multidisciplinary team. Scores across all six CRS-R subscales will be documented. Diagnostic classification will be based on the highest level of reproducible behavioral response observed during repeated assessments.

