From a public health perspective, the potential relevance of this work extends beyond individual-level assessment. Advanced neuroimaging techniques such as fMRI and FDG-PET, while informative, are costly, resource-intensive, and often inaccessible in low and middle-income settings. EEG-based paradigms that can be implemented at the bedside offer a more scalable and equitable approach to DoC research. If feasibility and systematically characterizable neural responses are demonstrated, this line of research may contribute to the development of accessible assessment strategies aligned with public health priorities of feasibility, equity, and responsible resource utilization.

Several limitations of the present protocol should be acknowledged. The relatively small sample size and single-center design limit generalizability and preclude conclusions regarding diagnostic performance or individual-level classification. Moreover, interoceptive processing may be influenced by factors such as medication exposure, autonomic dysfunction, and gastrointestinal comorbidities, which will require systematic control in future studies. In addition, this protocol is not designed to establish causal relationships between interoceptive neural responses and conscious awareness. These considerations underscore the exploratory nature of the present work and highlight the need for subsequent multicenter and longitudinal investigations with larger cohorts and predefined validation frameworks.

Importantly, this protocol is intended to serve as an initial methodological step within a staged translational research pathway rather than as a diagnostic validation study. The primary objective is to establish feasibility, tolerability, and signal-level characteristics of gut-related interoceptive EEG responses under standardized bedside conditions, thereby generating essential methodological parameters and effect size estimates to guide subsequent multicenter and hypothesis-driven investigations.

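### The UWS-MCS effect size can partly reflect type and age of brain injury, because the planned one-way ANOVA uses neither and the limitations name neither

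*Protocol article*

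**What the plan says.** **Who enters.** Criterion 1 of Table 1 (section 2.2) takes "Patients with chronic-phase disorders of consciousness (DoC) (duration ≥28 days" or more, "due to etiologies such as traumatic brain injury, stroke, or cardiac arrest". The list of causes is open, and duration has a lower limit but no upper one.

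**How the groups are formed.** "The target sample size is 15 participants per group". Section 2.3 assigns UWS or MCS by behaviour: "Diagnostic classification will be based on the highest level of reproducible behavioral response observed during repeated assessments". The only matching stated is for the "age and sex-matched healthy controls (HCs"; nothing is said about making UWS and MCS alike.

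**How they are compared.** Section 2.6: "Group-level comparisons among UWS, MCS, and healthy control participants will be performed using one-way ANOVA", one for each electrophysiological outcome, followed by Tukey HSD for the pairs. Group is the only factor. Effect sizes are to be reported for the design of confirmatory studies.

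**What is acknowledged.** The limitations in section 3 list "factors such as medication exposure, autonomic dysfunction, and gastrointestinal comorbidities" as possible influences on interoceptive processing. Etiology and time since injury are not in that list.

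**The concern.** UWS and MCS are not randomised groups. A hypoxic injury and a focal traumatic or vascular one may affect the cortical response to rectal distension differently, and so may one month against several years since injury. If either factor is distributed differently between UWS and MCS, the observed difference in ERP or ERSP mixes level of consciousness with kind and age of injury.

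The age and sex matching of controls does not help, because these variables exist only in patients. For the same reason they cannot simply be added to the three-group ANOVA, since controls have no value for them.

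What is at stake is mainly the effect estimate. Sections 2.6 and 2.7 intend it for the planning of later studies, so a confounded UWS-MCS difference would be carried into their sample sizes and hypotheses.

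**Working it through.** **1. The plan's own figure.** Section 2.5 gives d = 1.13, two-tailed α = 0.05, 80% power and 13 per group. By the normal approximation, n = 2(1.960 + 0.842)²/1.13² = 12.3, so 13 per group. With the exact noncentral t, power is 78.9% at 13, 82.1% at 14 and 84.8% at the target of 15. The figure reproduces to within one patient per group, and the point here does not depend on it.

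**2. Inputs for the bias.** From the documents: 15 per group, one-way ANOVA, Tukey HSD. Not in the documents, and therefore assumed: the share of one etiology in each group (p_U, p_M) and its effect g on amplitude, in units of the within-etiology SD. The true UWS-MCS difference is set to zero.

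**3. Bias of the unadjusted difference.**
- Spurious difference = g × (p_U − p_M).
- Spurious d = that difference divided by √(1 + g² × [p_U(1 − p_U) + p_M(1 − p_M)]/2).
- For 50% v 20% the bracket is 0.25 + 0.16 = 0.41, half of which is 0.205.

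| g (SD) | Spurious difference (SD) | Spurious d | False positives, planned Tukey contrast | False positives, single t-test at 5% |
|---|---|---|---|---|
| 0.5 | 0.5 × 0.3 = 0.15 | 0.15/√1.051 = 0.15 | about 3% | about 7% |
| 1.0 | 1.0 × 0.3 = 0.30 | 0.30/√1.205 = 0.27 | about 6% | about 11% |
| 1.5 | 1.5 × 0.3 = 0.45 | 0.45/√1.461 = 0.37 | about 11% | about 17% |

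The false-positive rates are simulated, with controls given unit SD. The Tukey column is the one that describes this plan. Its reference value is about 2%, because Tukey spreads a 5% familywise error over three pairs.

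**4. Sensitivity to the assumed shares.** At 60% v 20% and g = 1.0 the spurious difference is 0.40 SD and the Tukey rate about 10%. At 40% v 20% and g = 1.0 the difference is 0.20 SD. With equal shares there is no bias. Time since injury would act in the same way.

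**5. Cost of adjusting.** A patients-only comparison of 15 and 15 has 28 degrees of freedom, and two covariates leave 26. For a single test at d = 1.13, power is 84.8% unadjusted. With two covariates it is 84.6%, 81.1% and 75.9% at variance inflation of 1, 1.1 and 1.25, before any gain from variance that the covariates explain.

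**The case against.** **The contrast is exploratory and the causal claim is disclaimed.** Section 2.7 ranks group comparisons as secondary and exploratory, section 2.5 calls them descriptive, and section 3 says the design cannot establish a causal link between neural responses and awareness. This stands and keeps the severity down. It does not remove the point, because a disclaimer does not correct a biased effect estimate, and that estimate is what the plan hands on.

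**An adjusted analysis may be in an unseen SAP.** This stands in part: nothing in the article excludes one. But the article itself fixes the recruitment criteria and an unadjusted comparison, and it lists its known influences without these two.

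**Stronger readings that the documents do not support:**
- *That UWS-MCS is the only analysis bearing on level of consciousness.* Section 2.7 also plans associations of EEG markers with CRS-R total and subscale scores. These are open to the same confounding.
- *That chance imbalance is itself a bias.* If one etiology makes up a third of both populations, groups of 15 differ by four or more such patients in 17% of samples. That is ordinary sampling variation, and a single t-test keeps its error rate of about 5%.
- *That the false-positive rate is 7% to 17% against 5%.* Those are single-test figures; the plan uses Tukey.
- *That recruitment must be balanced by etiology.* Section 2.3 fixes the category only after enrollment, from at least five CRS-R assessments over a week. A quota could mean turning away patients already consented at a single centre.
- *That the adjusted effect size should replace the unadjusted one.* Section 3.1 foresees more heterogeneous cohorts, for which the unadjusted figure may be the relevant one.

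**Conclusion.** The point holds as a weakness of the planned UWS-MCS comparison: open etiologies, no upper limit on duration, groups formed by behaviour, and an analysis that uses neither factor. The effect size can partly reflect type and age of injury. The documents do not show that it will, in which direction, or by how much.

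Under the assumed 50% v 20% split and an effect of 0.5 to 1.5 SD, the spurious d is 0.15 to 0.37, that is, 13% to 33% of the planning value of 1.13 (0.15/1.13 and 0.37/1.13). The Tukey contrast is then falsely positive in about 3%, 6% and 11% of studies against about 2%. Shares and effect are illustrations only.

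Minor to moderate: the contrast is secondary and exploratory, and the primary aim of feasibility is untouched.

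**What to change.** 1. Tabulate etiology and days since injury by group. Checking criterion 1 already requires both, so no new data are needed.
2. Keep the planned ANOVA. Beside it, as a sensitivity analysis, report the UWS-MCS contrast from a patients-only linear model with a coarse etiology term (for example hypoxic v other) and log days since injury. Treat the CRS-R associations in the same way.
3. Give both the unadjusted and the adjusted effect size for later planning.
4. Add etiology and time since injury to the limitations in section 3.

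**Cost.** Analysis and reporting text only; no recruitment quota is required. The adjusted model spends 2 of 28 degrees of freedom and may lose some precision: single-test power at d = 1.13 goes from 85% to between about 76% and 85%. Confounding within the coarse etiology classes, such as the mix of trauma and stroke, would remain and should be stated.
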